| Background | One in three Medicare enrollees received their insurance beneﬁts through Medicare Advantage (MA) plan.^1^ After the passage of the Medicare Modernization Act, there has been a rapid increase in MA enrollment and use of skilled nursing facilities (SNF) for post-acute rehabilitation services compared to inpatient rehabilitation facilities. Previous studies examining utilization of rehabilitation services and the quality of care have focused on Medicare fee-for-service (FFS) patients.^2^ However, there is no information about the rehabilitation quantity, quality, and outcomes of care among MA patients staying in SNF. The Office of Inspector General reported that SNFs upcode the FFS patients into higher payment RUGs categories, leading to more hours of therapy without a substantial rise in case-mix (age and diagnoses at admission were largely unchanged from 2006 to 2008).^3^ It is unknown whether this inappropriate selection of higher paying RUG therapy group in SNFs is affecting MA patients or not and how it influences the clinical outcome in these two groups. Our group has recently published a paper about rehabilitation service utilization in patients with hip fracture among Medicare FFS beneficiaries.^2^ Jung et al. reported that there is an increase in the quantity of therapy among FFS patients with hip fracture without change in case mix at SNF admission.^2^ [name] is interested in extending this research in the MA population and comparing this with traditional FFS patients. Initially, we thought of using MDS-3 assessment completed on all Medicare- or Medicaid-certified nursing home residents irrespective of their insurance status. However, after doing a comprehensive literature review, we found that hospitals receiving a disproportionate share and educational training payments and supplements submit claims for MA beneficiaries.^4^ Therefore, we decided to use inpatient claims and HEEDIS for retrieving hospital related information. |

| **Data Sources** | **Variables** | **Link** | **Years** |
| --- | --- | --- | --- |
| Medicare Provider and Analysis Review (MedPAR) | Types of Fracture, Hospital length of stay, ICU, HCC score, hospital acquired conditions, and fracture management using ICD-9 procedure codes. | <https://www.resdac.org/cms-data/files/medpar-rif> | 2010-2015  Year 2010 was used to look back |
| Minimum Data Set (MDS 3.0) | Admission and Discharge ADL, Pain Status, Cognition, Pain, BMI | <https://www.resdac.org/cms-data/files/mds-3.0> | 2010-2015 |
| Master Beneficiary Summary File (MBSF) | Age, Sex, Race, Marital Status, Date of death, Enrollment Status: FFS, MA, dual eligibility | <https://www.resdac.org/cms-data/files/bsf> | 2011-2015 |
| Online Survey, Certification, and Reporting System (OSCAR) | SNF Characteristics, Profit Status, Part of Chain, Staffing Pattern: Total RN/LPN FTE, PT- FTE, OT-FTE, MD-FTE | <http://www.longtermcareinfo.com/data/casper-and-oscar.php> | 2011-2015 |
| Healthcare Effectiveness Data and Information Set (HEDIS) | Capture readmission for MA patients ‘if patients will readmit to non- DSH hospitals | <https://www.resdac.org/cms-data/files/hedis-puf> | 2011-2015 |
| American Community Survey | Zip code level median household income and education. | <https://www.census.gov/programs-surveys/acs/> | 2011-2015 |
| Residential History File (RHF) | Successful Discharge to the Community | RHF create a per-person chronological history of health service utilization and location of care within a pre-specified calendar using Medicare claims and post-acute assessment data.  <https://www.ncbi.nlm.nih.gov/pmc/articles/PMC3015013/> | 2011-2015 |

**Note:** These are person-level data (i.e., MDS, MBSF, MedPAR, and HEDIS) are covered under the strict terms of a Data Use Agreement (DUA) with the Centers for Medicare and Medicaid Services (CMS). We are prohibited from making any person-level data file, no matter how de-identified, available. However, researchers interested in replicating the results of these analyses may enter into their own DUA with CMS. Please contact the Research Data Assistance Center (ResDAC) at www.resdac.org for assistance. The OSCAR/CASPER is provider-level data, and zip-code level data from the American Community Survey are available for purchase/download. **Links are provided in the table above for more information.**

**Abbreviation:** FFS- Fee-for-Service; MA- Medicare Advantage; SNF- Skilled Nursing Facilities; HCC- Hierarchical Condition Category; ICU- Intensive Care Unit; ICD-9- International Classification of Diseases, Ninth Revision, Clinical Modification (**ICD**-**9**-CM);

ADL- Activities of Daily Living; BMI- Body Mass Index; Total RN/LPN FTE- Total number of full-time equivalent Registered Nurse and Licensed Practical Nurse; Total PT- FTE- Total number of full-time equivalent Physical Therapist; Total OT- FTE- Total number of full-time equivalent Occupational Therapist; Total MD- FTE- Total number of Full-time Physician;

DSH- Disproportionate Share Hospital,

**Timeline**:

| **Date** | **Proposed Activities** |
| --- | --- |
| November 2016 | First meeting to discuss research question- [name], a postdoc fellow, presented his research ideas and hypothesis in our regular research meeting. |
| December 2016 | Comphrensive literature review |
| January 2017 | Presented research strategy with literature review |
| February 2017 | Data retrieval and proposal drafted |
| February 2017 | Analytical cohort created |
| March 2017 | Descriptive Analysis completed |
| March 2017 | Discuss results with clinician and coauthors |
| April 2017 | Try to develop instrumental variable but could not able to find good one |
| April 2017 | Propensity Score Matching and then decided to use IPTW |
| May 2017 | Presented final analysis after using IPTW weights and SNF fixed effects |
| May 2017 | Present the results in Annual PO advisory board meeting |
| June 2017 | Sensitivity Analysis to compare long term risk: 6 moths and 1year mortality |
| July 2017 | First draft of manuscript including all tables and figures |

| **Study Retrieval Request** | |
| --- | --- |
| Data Requested | November 14 2016 |
| Analytical Cohort Completed | February 2017 |
| Unit of Analysis | Individual level |
| Research Questions | 1. Evaluate the differences in post-acute rehabilitation services utilization (physical therapy, occupational therapy) in older patients enrolled in Medicare health maintenance organizations (HMOs) and fee-for-service (FFS) systems during a short stay in skilled nursing facilities (SNFs). 2. Compare the differences in patients centered outcome associated with amount of rehabilitation services utilization during a short stay in skilled nursing facilities (SNFs). |
| Working Hypothesis | FFS patients will be receiving more rehabilitation therapy and staying longer in the SNF, and will have better outcomes. |
| Study Sample | We will select patients with a hip fracture for this study because this is an acute condition that commonly occurs in frail older adults and majority if them receives rehabilitation care in the SNF. |
| **Inclusion Criteria** | **Dataset: MedPAR Year:** January 2010 (lookback period for 2011) through June 2015  Patients admitted to hospital with hip fracture  MS-DRG codes: 533, 534, 535, and 536  Primary ICD-9-CM diagnostic codes: 82000, 82021, 82022, 82023, 82024, 82026, 82027, 82028, 82029, 82030, 82031, 82032, 8208, 82080, 82009, and 8080  Age ≥ 65 years  Patients from hospital with no information on disproportionate share  Length of stay less than 15 days  Discharged to only SNF  Admitted to SNF within 3 days of discharge from hospital  Merge with American community Survey  Exclude previous nursing home stay in past twelve months  Exclude previous hospitalization in past twelve months  **Dataset: MDS-3** - **Inclusion Criteria**  First-time SNF admissions from acute care hospitals identified on the basis of the presence of an MDS admission assessment tracking record  Include short term and long-term stay  Patients must have at least two assessments.  Patients must have first MDS assessment within 10 days of admission to SNF  Patients must have at least second or subsequent MDS (last) assessment within 10 days of discharge from SNF or any assessment.  Exclude Patients in coma  Exclude patients’ with any missing information on variables  Exclude patients’ with extreme therapy minutes and outliers  Exclude patients’ from Hawaii, Virgin Island, and Puerto Rico  Since 2008, the MedPAR file contains claims information on MA enrollees receiving care in disproportionate share hospitals (DSH) and Indirect Medical Education or Direct Medical Education adjustments. Therefore, our study cohort will be limited to patients discharged from these hospitals. |
| **Primary Independent Variable** | **Physical therapy (PT) and Occupational Therapy (OT)**  OT/PT Individual Minutes Number: The data in this column indicates the total number of minutes that physical therapy was administered to the resident in the last seven days.  OT/PT Concurrent Minutes Number: The data in this column indicates the total number of minutes that physical therapy was administered to the resident concurrently with one other resident in the last seven days.  OT/PT Group Minutes Number: The data in this column indicates the total number of minutes that physical therapy was administered to the resident as part of a group of residents in the last seven days.  **Measure of Rehabilitation Therapy:** We will have an average mean number of minutes of therapy per week, on the basis of the 7-day retrospective period and all assessments from the entire SNF stay. We will sum total number of individual minutes, concurrent minutes, and group minutes for PT and OT services across all MDS assessment records during patients’ entire SNF stay. Since most stays will be less than 40 days, we will calculate minutes of therapy received in the first 40 days of SNF stays. Further, we will compute average daily minutes per day by dividing the total number of therapy minutes from the SNF length of stay up to 40 days.  **SNF Length of stay** will be defined as calendar days from admission to discharge using MDS admission and discharge records. We will follow-up to 180 days in the SNF. |
| **Dependent Variables** | **Function:** Functional status will be measured using seven ADL items into a 28-point scale with 0 indicating independence and 28 indicating total dependence. Change in functional status will be computed by subtracting admission from discharge scores; negative scores will be reversed to be positive to improve understanding. The more positive score the greater the improvement.  **Hospital Readmission (yes/no):** We will use all-cause readmission to the hospital within 30 days following discharge from the index hospitalization. Because MA enrollees may be readmitted to a non-DSH hospital which may not submit claims to Medicare, so we will merge the MedPAR and HEDIS files to estimate the 30-day hospital readmission for MA enrollees.  **Long-stay resident (yes/no):** SNF patient will become a long-stay nursing home resident, if they will stay in a nursing home more than 100 days.  **Successful Discharge to the community (yes/no):** Successful discharge from SNF will be defined as being discharged to the community within 100 days of SNF admission and remaining alive in the community without being institutionalized in any acute and post-acute settings for at least 30 days. We will link MDS with MedPAR and HEDIS files to estimate the Successful discharge to the community. |

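### The ICD-9-CM code list does not consistently define hip fracture: it skips parts of the 820 family, holds entries that appear to match no code, and adds 8080 from outside the family

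*Protocol*

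**What the plan says.** The Study Sample row of the Study Retrieval Request names the population: "We will select patients with a hip fracture for this study". No subtype is set aside there.

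The MedPAR part of the Inclusion Criteria turns this into a selection rule. It opens with "Patients admitted to hospital with hip fracture" and gives two selectors one after the other. The first is "MS-DRG codes: 533, 534, 535, and 536". The second is a list of primary ICD-9-CM diagnosis codes: "82000, 82021, 82022, 82023, 82024, 82026, 82027, 82028, 82029, 82030, 82031, 82032, 8208, 82080, 82009, and 8080". The protocol defines none of these codes, gives no reason for any of them, and does not say whether a patient must meet both selectors or either one.

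Fracture details are used later in the design. The Data Sources table draws "Types of Fracture, Hospital length of stay, ICU, HCC score" and other items from MedPAR. The propensity model under Original Statistical Analysis includes fracture treatment but has no term for fracture type. Table 1 reports six treatment categories, among them partial and total hip replacement.

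**The concern.** The ICD-9-CM list is the only diagnosis-level definition of the study population. Its gaps follow no rule that the protocol states, such as closed fractures only or one anatomical site only. If hip-fracture codes are missing, patients who fit the stated population are never extracted, and weighting cannot bring them back. If a code for another fracture is present, those patients can be counted as hip fractures, and the listed propensity model has no fracture-type term to separate them.

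What is at stake is whom the cohort represents and whether it can be reproduced. The note under the Data Sources table points other researchers to their own data agreement if they wish to replicate the work. Anyone who applied this list as printed would inherit its gaps.

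**Working it through.** **Inputs.** The 16 entries and the four MS-DRG codes come from the Inclusion Criteria. The reference set is an assumption, because the protocol names ICD-9-CM but does not reproduce it: 820.00-820.03, 820.09, 820.10-820.13, 820.19, 820.20-820.22, 820.30-820.32, 820.8 and 820.9, which is 5 + 5 + 3 + 3 + 1 + 1 = 18 codes. The protocol gives no figure on this point to reproduce.

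**Step 1: what the list shows without a code book.**
- 15 of the 16 entries begin with 820; 8080 does not.
- After 82000 the list jumps to 82021. Only 82009, out of order near the end, falls in between. Nothing else from 82001 to 82020 appears, and neither does 8209.
- 82000 and 82030 are listed but 82020 is not, although 82021 and 82022 are.
- The 8202x run reaches 82029 but skips 82025.
- A four-digit code (8208) and a five-digit extension of it (82080) both appear.

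**Step 2: comparison with the assumed 18 codes.**

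| Block | Assumed codes | Listed | Omitted | Listed but matching no code |
| --- | --- | --- | --- | --- |
| 8200x | 5 | 82000, 82009 | 82001, 82002, 82003 | none |
| 8201x | 5 | none | 82010-82013, 82019 | none |
| 8202x | 3 | 82021, 82022 | 82020 | 82023, 82024, 82026-82029 |
| 8203x | 3 | 82030-82032 | none | none |
| 8208 | 1 | 8208 | none | 82080 |
| 8209 | 1 | none | 8209 | none |
| Total | 18 | 8 | 10 | 7 |

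Omitted share by code count: 10/18 = 56%. The entries reconcile: 8 matching + 7 not matching + 1 outside 820 (8080) = 16.

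**Step 3: does an open/closed rule explain the gaps?** On the same assumption, the open codes are 8201x, 8203x and 8209 (5 + 3 + 1 = 9) and the closed codes are 8200x, 8202x and 8208 (5 + 3 + 1 = 9). The list holds 2 + 2 + 1 = 5 of the 9 closed codes and 0 + 3 + 0 = 3 of the 9 open codes. It is therefore neither the whole family nor the closed codes alone.

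**Step 4: the two ways of combining with the MS-DRG codes.**
- If both selectors are required (AND), every patient with an omitted primary code is excluded. An 8080 patient enters only if the DRG is also 533-536.
- If either suffices (OR), a patient with an omitted code can still enter by DRG, so the loss is smaller. Every 8080 patient passes this step on the diagnosis alone.

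Let *p* be the share of hip-fracture admissions that carry an omitted code. The share lost at this step is *p* under AND and lies between 0 and *p* under OR. The protocol gives no frequencies by code, so *p* is unknown. Neither reading removes both defects.

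**The case against.** The strongest objection is that the code meanings lie outside the protocol. That seven entries match nothing, that the family has 18 codes and that 8080 is acetabular all rest on the classification. This stands, so those statements are given here as an assumption to be checked. The irregularities in Step 1 do not depend on it.

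The list may also be a transcription slip rather than the code that was run. The protocol cannot settle this. Even so, the protocol would then misstate the cohort and would need correcting.

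A reader might infer more than the protocol supports:
- *That the list as a whole selects the wrong patients.* Entries that match no code select nobody, and omitted codes lose eligible patients. Only 8080 could bring in a different fracture.
- *That femoral-neck fractures are left out.* On the assumed code set they are only partly omitted: 82000, 82009 and 8208 are present. One omitted code, 82020, is trochanteric. The direction of any shift in case mix cannot be derived.
- *That a given percentage of patients is lost.* The 56% counts codes, not patients.
- *That the FFS-MA contrast is biased.* The same list applies to both groups, and fracture treatment is in the propensity model. Bias through this route would require coding, or the effect of plan among the patients lost, to differ in a way that the protocol does not address.

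**Conclusion.** The concern holds in a limited form. As written, the ICD-9-CM list does not consistently define the stated population. The gaps, the paired 8208 and 82080, and the presence of 8080 can be seen in the text itself. Assuming the standard 18-code family, 8 codes are listed, 10 are omitted, 7 entries are inert, and 8080 is a pelvic fracture.

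The consequence is under-coverage that depends on coding specificity. On that code set, a neck fracture coded to 82000 or 8208 meets the diagnosis criterion, while one coded to 82002 or 82003 does not. One other fracture type may also be included. How far this changes the cohort depends on the unstated AND/OR rule and on code frequencies that the protocol does not give. The harm shown is to representativeness and reproducibility, and no bias in the FFS-MA comparison is shown. The list should be corrected.

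**What to change.** 1. Check the list against ICD-9-CM and compare it with the code actually run.
2. Replace it with the complete 820 family: 820.00-820.03, 820.09, 820.10-820.13, 820.19, 820.20-820.22, 820.30-820.32, 820.8 and 820.9. If open fractures are not wanted, drop 820.1x, 820.3x and 820.9 together and say so.
3. Remove the entries that match no code.
4. Remove 8080, or give a reason for keeping it.
5. State whether the list combines with MS-DRG 533-536 by AND or OR.
6. Re-extract the cohort, report counts by code, and rerun the propensity weights, models and tables.

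The data are already held, so no new collection is needed. The cost is more than a new extraction, however. The Timeline shows the analytical cohort built in February 2017 and the manuscript drafted in July 2017, so linkage, weighting and all results would have to be repeated and the cohort counts would change. If step 1 shows that the program used a correct list, only the protocol text needs amending.

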**Original Statistical Analysis**

There are some evidence showing cherry picking of healthier beneficiaries in MA plans and sicker patients switching from MA to FFS. There might be a level of endogeneity in the selection of MA enrollees. We anticipated that MA and FFS beneficiaries might differ with respect to demographic, clinical, and socioeconomic characteristics. To account for differences in observed demographic and clinical characteristics between FFS and MA, we will generate a propensity score that will reflect the probability of individuals to be in MA versus FFS program using observable baseline characteristics. Propensity score model will include age, gender, race, marital status, length of stay in the hospital, number of days in the intensive care unit, fracture treatment, number of comorbidities, admission cognition, body mass index, hospital-acquired complications, HCC score, dual Medicare/Medicaid status, median household income, household education and state fixed effects. After that, Inverse Probability of Treatment Weighs (IPTW) will be generated from the propensity scores to balance the differences in patient demographic and clinical characteristics.

We will compare baseline characteristics between FFS and MA using chi-square tests for categorical variables and t-tests for continuous variables then weights were applied to calculate weighted rates and mean. First, we will use linear probability model without applying IPTW to compare the difference in outcomes between MA and FFS and then we will use IPTW.

After that, we will use a linear probability model to compare outcomes between FFS and MA patients after applying IPTW and SNF fixed-effect.

**After reviewer feedback:** We added odds ratio from logistic regression models to compare the binary outcome variables for 30-day hospital readmission, becoming a long-stay resident and successful discharge to the community.

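### The 12-month prior-hospitalisation exclusion is one written rule, but MedPAR ascertains it unequally for FFS and MA patients; separately, the disproportionate-share inclusion line contradicts the closing cohort restriction

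*Protocol*

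**What the plan says.** In the Study Retrieval Request table, the Inclusion Criteria row lists under the MedPAR data set: "Exclude previous hospitalization in past twelve months". The same list carries, without the word 'exclude', "Patients from hospital with no information on disproportionate share".

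The row closes by explaining the data: "Since 2008, the MedPAR file contains claims information on MA enrollees receiving care in disproportionate share hospitals (DSH) and Indirect Medical Education". That sentence goes on to name the direct form of the teaching adjustment as well. The row then draws the consequence: "Therefore, our study cohort will be limited to patients discharged from these hospitals".

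The Dependent Variables row recognises that some MA stays are missing, but in the context of readmission: "Because MA enrollees may be readmitted to a non-DSH hospital which may not submit claims to Medicare". Its remedy there is to combine HEDIS with MedPAR for the MA readmission estimate. The same row also links HEDIS for successful discharge to the community.

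The data-source table gives MedPAR for 2010-2015, with 2010 as the look-back year. HEDIS and the Master Beneficiary Summary File (MBSF, the source of enrolment status) are given for 2011-2015. Original Statistical Analysis notes evidence of "sicker patients switching from MA to FFS" and lists the propensity covariates. Prior hospitalisation is not among them.

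**The concern.** The exclusion is meant to leave patients with no recent hospital stay in both arms. It can do so only where the stay can be seen. The closing restriction concerns the hospital of the index discharge. It says nothing about where a patient was admitted in the preceding year, so an MA patient's prior stay at a non-submitting hospital leaves no MedPAR record.

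Recent hospitalisation plausibly predicts readmission, long-stay residence and failure to return to the community. If the MA arm keeps some of these patients and the FFS arm removes them, part of the payer contrast reflects cohort construction. Switchers aside, the distortion makes MA look worse, which is also the direction of the working hypothesis that FFS patients will have better outcomes.

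**Working it through.** The protocol gives no figure to reproduce on this point, so the check is by reading, followed by an illustration with assumed inputs.

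**Step 1: what each arm's look-back can see.**

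| Prior stay in the last 12 months | FFS at the time | MA at the time |
|---|---|---|
| At a DSH or medical-education hospital | seen, patient removed | seen, patient removed |
| At another hospital | seen, patient removed | may not be seen, patient kept |

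Full FFS capture is an inference. The protocol treats missing claims as a problem of MA stays only, but does not state that FFS capture is complete.

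**Step 2: whether another source fills the gap.** HEDIS is named for readmission and successful discharge. The Background also says in general terms that inpatient claims and HEDIS supply hospital-related information, but nothing assigns HEDIS to the exclusion. On dates, index admissions run from January 2011 to June 2015, which is 54 months. For the 12 months of 2011 the look-back reaches into 2010, which the listed HEDIS years do not cover. For the remaining 54 − 12 = 42 months the look-back falls within the listed years.

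**Step 3: whether weighting repairs it.** Every retained patient is recorded as having no prior stay, so the variable is constant in the data and could not be added to the propensity model. Correlated covariates (age, number of comorbidities, cognition, body mass index, hospital and intensive-care days, HCC score) can absorb part of the difference. HCC score is itself listed as a MedPAR variable, so its capture may also differ by payer. SNF fixed effects compare patients within a facility and do not remove a patient-level difference there.

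**Step 4: illustration.** Let p be the share of patients with a prior-year stay and q the share of those in MA whose stay is unseen. Neither is in the documents. The share of retained MA patients with an unseen prior stay is

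pq / (1 − p + pq)

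| p | q = 10% | q = 20% | q = 30% |
|---|---|---|---|
| 20% | 0.02/0.82 = 2.4% | 0.04/0.84 = 4.8% | 0.06/0.86 = 7.0% |
| 30% | 0.03/0.73 = 4.1% | 0.06/0.76 = 7.9% | 0.09/0.79 = 11.4% |
| 35% | 0.035/0.685 = 5.1% | 0.07/0.72 = 9.7% | 0.105/0.755 = 13.9% |

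If these patients' readmission risk is 4 to 8 points higher (also assumed), the MA rate rises by 2.4% × 4 = 0.10 points at the low end and 13.9% × 8 = 1.11 points at the high end. The middle case is 7.9% × 6 = 0.47 points.

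With wider assumptions (p up to 40%, q up to 40%), the share reaches 0.16/0.76 = 21.1%. At a base risk of 10% and a relative risk of 1.3 to 2.0, the shift then spans about 0.1 to 2.1 points.

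**Step 5: switchers.** These are gross figures. If a fraction s of FFS patients with a prior stay had it while enrolled in MA, the FFS arm keeps a share spq / (1 − p + spq). With equal p and q in both arms, the net difference shrinks as s grows and vanishes only at s = 1. The documents give no value for s.

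**Step 6: the DSH line.** Read literally as an inclusion criterion, it admits hospitals with no DSH information. The closing restriction limits the cohort to hospitals with DSH or medical-education adjustments. A hospital with neither is admitted by one sentence and barred by the other. A teaching hospital without DSH data satisfies both as written, but would be lost if the line were simply turned into an exclusion.

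**The case against.** Several points on the other side stand.

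- A reader might infer that the two cohorts are built by different rules. They are not: the rule is identical and only its ascertainment differs.
- A reader might infer that HEDIS serves readmission alone and could not help. It is also linked for successful discharge, and its listed years cover the look-back for index admissions from 2012 on. The narrower statement is that the plan does not assign it to the look-back.
- It is tempting to say the FFS arm is left with no prior stays at all. The protocol's own remark on switching argues against that, because a switcher's MA-period stay has the same blind spot.
- It is also tempting to say that weighting cannot touch the problem. The covariates include markers of frailty, and cognition and body mass index come from MDS, which is completed irrespective of insurance. Partial adjustment is likely; full adjustment is not shown.
- The adjacent exclusion of prior nursing-home stays, if taken from MDS, would already remove some MA patients whose unseen admission led to such a stay.
- The low end of the illustration is negligible, and every input to it is assumed.

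On the DSH line, a reader might infer that it produces a payer-specific cohort. The closing restriction applies to both payers alike and the line is probably missing a word, so it is a separate drafting conflict.

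None of this makes an MA stay at a non-submitting hospital visible to the look-back.

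**Conclusion.** The concern holds in a limited form. Followed as written, the plan screens prior hospitalisation less completely in MA than in FFS, and it recognises the same data gap only for two outcomes. That rests on the protocol's text, plus the inference that FFS stays are captured.

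The size is not known. About 2-14% of retained MA patients under the main assumptions, and roughly 0.1 to 1.1 points on readmission, are illustrations before any offset from switchers, partial adjustment by weighting, or the nursing-home exclusion. The expected direction is against MA, but the net direction is not proven.

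The contradiction on DSH hospitals is certain as a matter of text. It matters because it defines the cohort and the protocol invites others to replicate the analysis.

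**What to change.** 1. In both arms, count prior admissions only at hospitals that submit MA claims (those with DSH or medical-education adjustments). Make this the main look-back, or at least a sensitivity analysis. A stay elsewhere is then ignored whatever the payer. Any remaining imbalance comes only from MA and FFS patients differing in how often they have prior stays or use such hospitals.
2. Define payer at the index admission. Add a sensitivity analysis that excludes patients who changed payer in the prior 12 months. For index stays in 2011 this needs the 2010 MBSF, which is not among the listed years.
3. State whether HEDIS is used for the look-back and, if so, for which index years.
4. Reconcile the DSH line with the closing restriction, for example: *Exclude patients from hospitals that receive neither DSH nor IME/DME adjustments.* This keeps teaching hospitals that lack DSH data.

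Items 1 and 2 cost a cohort re-extraction, one more MBSF year, re-estimated weights and rerun tables; the Timeline shows the cohort completed in February 2017 and analyses run after that. Under item 1, some FFS patients with prior stays at other hospitals re-enter, so the cohort is less strictly free of recent hospitalisation. Item 3 is a sentence, unless HEDIS is newly brought into the look-back. Item 4 is a wording change if the extraction already followed the closing restriction.

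### The two-assessment and complete-data rules select one cohort on post-admission events, for outcomes of which only ADL change needs a second assessment

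*Protocol*

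**What the plan says.** The Inclusion Criteria (MDS-3 part) set these conditions on each patient:

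- "Patients must have at least two assessments".
- "Patients must have first MDS assessment within 10 days of admission to SNF".
- There must be a second or later "assessment within 10 days of discharge from SNF or any assessment".
- Patients "with any missing information on variables" are excluded, and no variable is named.
- Patients "with extreme therapy minutes and outliers" are excluded.

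No other section defines a separate cohort for any outcome. Recommended Tables 2 and 3 show one FFS column and one MA column throughout.

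The outcome definitions draw on different sources. For function, "Change in functional status will be computed by subtracting admission from discharge scores". Readmission is "all-cause readmission to the hospital within 30 days following discharge from the index hospitalization", and the plan will "merge the MedPAR and HEDIS files to estimate the 30-day hospital readmission for MA enrollees". SNF length of stay uses admission and discharge records. Long-stay status is a stay of more than 100 days. Successful discharge uses MDS linked to MedPAR and HEDIS, and the data-source table also lists the Residential History File for it.

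Under Original Statistical Analysis, the propensity score is built from baseline characteristics with state fixed effects. The outcome models then use the resulting weights, with and without SNF fixed effects.

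**The concern.** A second assessment can exist only after SNF admission, so the rule makes eligibility depend on follow-up. The readmission clock starts earlier still, at index hospital discharge. A patient who returns to hospital before a second assessment may leave both the numerator and the denominator of the readmission rate. A patient who dies early may leave the denominator. A patient who goes home early may drop out of length of stay and successful discharge.

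If these losses differ between MA and FFS, the contrast is distorted even when the true risks are equal. The protocol's working hypothesis expects FFS patients to stay longer, so a difference in the chance of reaching a second assessment is plausible. Three of the four outcomes in Table 3 are exposed to this, as is length of stay in Table 2.

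**Working it through.** **Which outcomes need a second assessment**

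| Outcome | Source in the protocol | Second assessment needed? |
|---|---|---|
| Change in ADL | Discharge minus admission score | Yes |
| 30-day readmission | MedPAR and HEDIS | No |
| SNF length of stay | Admission and discharge dates | No |
| Long-stay status | Stay of more than 100 days | No |
| Successful discharge | Linked MDS, MedPAR, HEDIS; Residential History File | No |
| Therapy minutes | Summed over MDS assessments | At least one, not two |

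**Timing.** SNF admission may follow hospital discharge by up to 3 days, and the first assessment may follow SNF admission by up to 10 days. The first assessment can thus fall as late as day 3 + 10 = 13 of the 30-day readmission window, with the second later still.

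**Can the analysis correct it?** The propensity score models membership of MA versus FFS from baseline data. SNF fixed effects compare patients within a facility. Neither models who reaches a second assessment. The one sensitivity analysis in the Timeline (6-month and 1-year mortality) is not described as relaxing the rule.

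**Size.** The protocol gives no exclusion counts or expected rates, so there is no figure to reproduce, and every input here is an assumption. Let r be the true 30-day readmission risk, e the share of readmitted patients excluded, and s the share of other patients excluded. Then

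observed risk = r(1 − e) / [r(1 − e) + (1 − r)(1 − s)].

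Take r = 0.18 in both groups, so the true difference is zero.

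*Only readmitted patients lost (s = 0):*

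- e = 0.15: 0.153 / (0.153 + 0.82) = 15.7%
- e = 0.25: 0.135 / (0.135 + 0.82) = 14.1%
- e = 0.35: 0.117 / (0.117 + 0.82) = 12.5%

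The false difference is 1.6 points for 15% versus 25% lost, and 3.2 points for 15% versus 35%.

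*Other patients lost as well:*

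- e = 0.15, s = 0.05: 0.153 / (0.153 + 0.779) = 16.4%
- e = 0.25, s = 0.15: 0.135 / (0.135 + 0.697) = 16.2%

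The false difference is about 0.2 points. If e = s within each group, the formula returns r and the difference is exactly zero.

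*Other true risks (s = 0):* for r from 10% to 20%, 20% versus 30% lost gives a false difference of about 0.9 to 1.8 points, and 20% versus 40% gives 1.9 to 3.6 points. The sign follows whichever group loses more.

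*Equal loss in both groups:* the contrast stays at zero but the level shifts. With r = 18%, e = 25% and s = 0, both groups show 14.1%.

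**The case against.** The best reply is that the protocol never says which MDS records count as an assessment. It mentions both an admission tracking record and MDS discharge records. If a discharge record counts, many patients who go home or return to hospital early still have two records and stay in. This stands. A reader might infer that early readmissions, deaths and short stays are certainly removed, but the text supports only that they can be. It does not remove the concern, because eligibility would still rest on data recorded after admission.

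Second, the complete-data rule names no variables. It stands that excluding patients for missing baseline covariates is not selection on a later event, and how such gaps are handled may belong in an analysis plan not shown here. The point concerns only the rule's open wording, which as written reaches discharge ADL.

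Third, the closing words of the last-assessment rule can be read as loosening selection, since an assessment near discharge would no longer be required. That is a fair reading. The wording leaves the 10-day window without clear force, so it needs resolving, but it does not settle which reading was meant.

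Fourth, therapy minutes also depend on assessments, and Research Question 2 links outcomes to the amount of therapy. This stands as a limit on the remedy: minutes need at least one assessment. The analysis section, however, compares outcomes by MA versus FFS membership, and that comparison requires neither minutes nor a second assessment.

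Fifth, the size is wholly assumed, and losses among other patients can shrink it almost to nothing. This also stands, and is why the range starts at zero.

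**Conclusion.** The concern holds in a bounded form. The protocol fixes one cohort whose entry rules depend on events after SNF admission and uses it for four outcomes that need no second assessment. The planned adjustment cannot undo that selection.

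The extent is open, because it turns on the undefined term assessment. Under an assumed readmission risk of 18% in both groups, the false difference runs from about 0 points, when losses among readmitted and other patients are similar within each group, to 1.6-3.2 points, when 15% versus 25-35% of readmitted patients are lost and no others. These figures illustrate the mechanism; they do not estimate the bias in this study.

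A reader might go further and infer that the rule favours MA, because MA stays are expected to be shorter. The documents do not support this. They give neither exclusions by group nor the timing of readmissions relative to assessments, and the sign reverses if FFS loses more.

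**What to change.** 1. Define the cohort at SNF admission for 30-day readmission, SNF length of stay, long-stay status and successful discharge: all patients who meet the hospital criteria and have an SNF admission record.
2. Apply the second-assessment, last-assessment and discharge-ADL requirements only to the ADL-change analysis.
3. Analyse therapy minutes in all patients with at least one assessment that records them.
4. State which MDS records count as an assessment, in particular whether a discharge record does, and resolve the closing words of the last-assessment rule.
5. Report exclusions by group and reason, and show the results with and without the two-assessment rule.

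The cost is a rebuild of the cohort from files already held and a rerun of the models, with no new data. Denominators will differ between outcomes, so Tables 2 and 3 need a count for each row.
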